### Study Arms and Randomization

Families are randomized into one of three intervention Arms: (1) EMI; (2) EMI+Virtual HV with a CHW+Video Feedback; and (3) EMI+Hybrid HV with a CHW+Video Feedback. All Arms receive 16 weeks (4 months) of EMI stress reduction and family meal tip messages via smartphones. Arms 2 and 3 additionally receive eight home visits by CHWs focused on family meal quantity and quality, a meal preparation activity, and video feedback on their family meal behaviors/patterns every-other-week for 16 weeks. Arm 2 receives all of these components virtually and Arm 3 receives these components half in person and half virtual (hybrid). In between weeks, families in Arms 2 and 3 complete a Try-it-Yourself activity to apply the new skills/behaviors they have been taught. All Arms receive an 8-week (2 months) maintenance phase allowing for progressively less support so they can increase self-efficacy and sustainability of behavior change.

Once participants complete their baseline data collection visit, they are randomized into one of three study Arms (n=175 per Arm). If households have multiple eligible children, one child is randomly selected to minimize bias that could affect generalizability due to parent selection. Randomization is stratified by five racial/ethnic groups (African American, Hispanic, Native American, Asian American, White; n≈105 per race group). Block randomization schedules were produced in PASS 2021 (Kaysville, Utah) to account for the racial/ethnic stratification. Schedules are maintained by the biostatistician to keep team members blinded.

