#### Blinding and Investigator Allocation Concealment.

As with most behavioral interventions, it is not possible to double blind this RCT. However, this study incorporates measurement staff and investigator blinding as much as possible to minimize bias. For example, the intervention is administered by CHWs who are not involved with measurement team responsibilities or meetings and measurement team members are blinded to participant study Arm assignment and are not involved with intervention team responsibilities or meetings. The biostatistician is the only completely unblinded member of the research team and will be overseeing data management and analyses throughout the trial and will have restricted access to the final study dataset.

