## STATISTICAL ANALYSIS PLAN

### Overview.

This study is powered for three pairs of tests [72] to evaluate intervention effectiveness: (a) Arm 2 vs. 1, (b) Arm 3 vs. 1, and (c) Arm 2 vs. 3 over three time points. Multi-level, general linear mixed models (MLMM) with a clinic random intercept that nests participants within clinics to address any clinic differences in the recruitment populations, with participant random slopes for time to examine intervention treatment effects, and conditional fixed effects regression models (within-child analytic contrast against baseline), are the primary analytical models for all study hypotheses. Participants’ randomized condition will be examined irrespective of adherence to the study protocol in accordance with an intent-to-treat (ITT) analysis. After the intervention has been fully administered, data will be assessed for balance across arms, outliers, missingness, and other modeling assumptions. Although randomization is expected to produce balance on measured and unmeasured characteristics, variables will be considered for inclusion as controls in adjusted analyses to reduce test statistic variance [73]. We expect little missing data based on our prior work, but if needed, we will employ methods recommended for clinical trials to minimize analytical assumptions required when missing data are present (e.g., follow up all randomized participants prior to unblinding [74], evaluating if results from the primary analysis differ when sensitivity analyses are performed [75]). Reasons for participant withdrawal and non-adherence will be analyzed and reported in the final ITT analysis [76].

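### The five race/ethnicity strata used to randomise appear in neither named primary model, and the covariates for adjusted analyses are left open next to an arm-balance check

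*Protocol article*

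**What the plan says.** **Randomisation.** Under Study Arms and Randomization: "Randomization is stratified by five racial/ethnic groups", with about 105 children per group, and block schedules produced "to account for the racial/ethnic stratification". Allocation is to three arms of 175.

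**Primary models.** The Overview of the Statistical Analysis Plan section names two. The first is "Multi-level, general linear mixed models (MLMM) with a clinic random intercept that nests participants within clinics", with participant random slopes for time. The second is described thus: "conditional fixed effects regression models (within-child analytic contrast against baseline), are the primary analytical models for all study hypotheses". Neither description mentions the strata. Race/ethnicity enters the analysis only under Sub-group Exploratory Analyses, as an interaction.

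**Covariates.** The same Overview says: "After the intervention has been fully administered, data will be assessed for balance across arms", along with outliers, missingness and modelling assumptions. The next sentence says that "variables will be considered for inclusion as controls in adjusted analyses to reduce test statistic variance". It gives no list and no selection rule.

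**Who is unblinded.** Under Blinding and Investigator Allocation Concealment: "The biostatistician is the only completely unblinded member of the research team and will be overseeing data management and analyses throughout the trial". Study Arms and Randomization adds that the biostatistician keeps the schedules.

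**The concern.** Two things are at stake.

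1. **Strata.** Blocking within strata balances the arms on race/ethnicity. If race/ethnicity predicts the outcome, a model without it leaves that variance in the error term although the design has removed it from the treatment contrast. The tests then become somewhat conservative, and some of the precision gained by stratifying is not used. The plan models clinic, which was not a stratification factor, and names no term for the factor that was.

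2. **Covariates.** Study Design gives four active months plus two maintenance months, and Aim 1 sets the primary endpoint at 6 months. Once the intervention has been fully administered, the primary-endpoint data therefore largely exist. If covariates are settled then, with allocation known, several adjusted estimates can be compared before one is reported. The trial was sized to hold an experiment-wise error of 0.05 over nine tests, and that control does not extend to an adjusted result chosen in this way.

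**Working it through.** **Inputs from Sample Size and Power Computations:** variance 18.8 (SD = √18.8 = 4.336), difference 1.67, two-sided z = 2.77 (p = 0.0056; 0.05/9 = 0.00556), 80% power, N = 525, 15% attrition. The ICC value is blank in the text as read.

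**The plan's own figure.** n per arm = 2(2.77 + 0.842)² × 18.8 / 1.67² ≈ 176, so 528 in all, against 525 planned. At 175 per arm, power is Φ(1.67/(4.336√(2/175)) − 2.77) = 79.8%. The simple formula therefore reproduces N when all 525 are analysed. With 15% loss, n = 525 × 0.85/3 = 148.75 per arm and power is 70.9%. The plan's calculation may use repeated measures through the missing ICC, so its statement about attrition can be neither confirmed nor called wrong. The 70.9% serves here only as a common starting point.

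**Effect of omitting the strata.** Let R² be the share of variance explained by the strata in the quantity on which arms are compared. R² is an assumption; the documents give no value.

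- Reported SE / true SE = 1/√(1 − R²)
- Actual per-test alpha = 2(1 − Φ(2.77/√(1 − R²)))
- With d = 1.67/(4.336√(2/148.75)) = 3.322, power without strata = Φ((d − 2.77)/√(1 − R²))
- Power with strata = Φ(d/√(1 − R²) − 2.77)

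| R² (assumed) | Reported SE too wide by | Actual alpha (nominal 0.0056) | Power without strata | Power with strata |
|---|---|---|---|---|
| 0 | 0% | 0.0056 | 70.9% | 70.9% |
| 2% | 1.0% | 0.0051 | 71.1% | 72.1% |
| 5% | 2.6% | 0.0045 | 71.4% | 73.8% |
| 10% | 5.4% | 0.0035 | 72.0% | 76.8% |

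**Simulation check.** The set-up was five strata of 105, blocks of six (assumed), 15% random loss, a baseline-to-follow-up correlation of 0.8 (assumed) and 5,000 runs.

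- Outcome level, strata explaining 10%: mean reported SE 0.1222 without strata and 0.1160 with, so 5.3% wider. The SE without strata exceeded the empirical SE (0.1189) by 2.7%, with Monte Carlo error of about 1/√(2 × 5,000) = 1%. Random loss undoes part of the balance, so the table is if anything on the high side for conservatism.
- Change from baseline, strata affecting level only: 0.0733 without and 0.0734 with. There is no widening.
- Change from baseline, strata explaining 5% of change: 0.0751 against 0.0733, about 2.5% wider.

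**Effect of free covariate choice.** A separate simulation used 149 per arm, no true effect and 2,000 runs. It took the most significant result over all subsets of 3 or 5 covariates, each explaining 2% or 5% of variance (assumed). Per-test type I error rose from 0.0056 to between 0.0095 and 0.019, with Monte Carlo error of about 0.002 to 0.003. Multiplied by nine tests, the Bonferroni bound moves from 0.05 to about 0.09 to 0.17. This is a worst case, because it assumes a full search and reporting of the best result as the main one.

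**The case against.** The best defence is that silence is not exclusion. The Overview lists no fixed effects at all, not even arm or arm-by-time, and a condensed article may leave them to a separate analysis plan. That stands as far as it goes: a missing covariate list alone would be no finding. What remains is that the article does give model structure, names clinic, does not name the randomisation factor, and gives race/ethnicity only an exploratory role.

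Several stronger readings are tempting, and the documents do not support them:

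- **Standard errors are certainly too wide.** They are wider only if strata predict the outcome, for which no figure is given. In the within-child model a time-invariant main effect drops out, so nothing is lost unless strata predict change.
- **Baseline adjustment would bring a very large gain.** A variance cut of r² (64% at r = 0.8) is measured against a follow-up-only comparison. The within-child contrast already uses baseline. Against a change score at r = 0.8, variance goes from 2(1 − 0.8) = 0.40 to 1 − 0.64 = 0.36, a gain of about 10%.
- **One unblinded analyst picks covariates on imbalance after follow-up ends.** The stated purpose is precision, not repair of imbalance. The timing is the end of the intervention, not of follow-up. No section says who chooses; oversight by the biostatistician is all that is stated.
- **Adjusted results replace the primary ones.** The open choice attaches to adjusted analyses, and their status is not stated either way.

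**Conclusion.** The point holds in a limited form. The strata used to randomise are in neither named primary model. The likely consequence is mild and in the conservative direction: about 1% to 5% on the standard error and roughly 1 to 5 points of power, for assumed R² between 2% and 10%. It is zero if strata do not predict the quantity compared. Type I error is not inflated by this omission.

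The covariate part matters more for credibility, but it is a vulnerability and not a planned misuse. An open choice follows an arm-balance check, at about the time primary-endpoint data exist, under an unblinded overseer. The Overview's own safeguard of completing follow-up before unblinding cannot cover that person. The inflation to 0.0095–0.019 per test applies only if a searched adjusted result is presented as the main one, which the text neither proposes nor rules out.

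Both parts are worth correcting because the correction is nearly free.

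**What to change.** - Include the five randomisation strata, with stratum-by-time terms, as fixed effects in the primary mixed model.
- Keep the baseline value in the model, either as a response or as a covariate, and say which.
- Add age and sex for neck circumference and HEI. BMI percentile is already age- and sex-specific.
- Fix this list, with a date, before anyone sees outcome data by arm.
- Label any other adjusted model a sensitivity analysis, and say that the balance check does not alter the primary model.
- Reconcile the reference to unblinding in the Overview with the statement that the biostatistician is unblinded throughout.

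The cost is wording. Race/ethnicity is needed to randomise, and age and sex to compute BMI percentile, so no new data are required. With three time points, the strata use 4 main-effect and 4 × 2 = 8 interaction parameters, 12 in all, against about 525 × 0.85 = 446 children.

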### Sample Size and Power Computations.

Study design features were accounted for in powering the study that required increases in sample size to minimize an inflated experiment-wise error rate (EER) due to three pairwise tests between each treatment arm for three primary outcomes (i.e., BMI%ile, neck circumference, and the Healthy Eating Index (HEI)). Accounting for these nine tests, sample size was determined using a conservative two-sided critical value of *z*=2.77 (*P*=0.006) to achieve experiment-wise Type I error of 0.05. Our power calculations were based on prior studies showing that a decline of two BMI%ile points was a clinically meaningful difference in children with overweight/obesity [46]. BMI%ile is a continuous outcome with a variance of 18.8. Eighteen-month follow up data with a comparable cohort provided intraclass correlation coefficient estimates to inform sample size determination (BMI%ile ICC ). At 80% power and multiple-outcome and pairwise testing corrected EER of 0.05, with a sample size of 525, we will be able to detect a minimum average difference in BMI%ile as small as 1.67 (or 0.38 SD) with 15% attrition. This magnitude translates to approximately a 2.8lb difference in a six year-old boy who is 3.8 feet tall and 45 lbs, or approximately a 7.5 ounce per month change in weight by the post-intervention endpoint.

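### If the nine-test cut-off z = 2.77 is also used for the final tests it is valid but gives up power; a three-group step-down within each outcome keeps 0.05 and recovers some of it

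*Protocol article*

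**What the plan says.** The Statistical Analysis Plan section of the protocol article states (Overview): "This study is powered for three pairs of tests", namely Arm 2 against 1, Arm 3 against 1 and Arm 2 against 3. Under Sample Size and Power Computations it says the sample size was raised to limit an "inflated experiment-wise error rate (EER) due to three pairwise tests between each treatment arm for three primary outcomes" (child BMI percentile, neck circumference and Healthy Eating Index). It goes on: "Accounting for these nine tests, sample size was determined" with a "conservative two-sided critical value of *z*=2.77 (*P*=0.006"), in order "to achieve experiment-wise Type I error of 0.05". The resulting claim is that the trial can "detect a minimum average difference in BMI%ile as small as 1.67 (or 0.38 SD) with 15% attrition".

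The cut-off appears only in the sample-size text. Neither the Overview nor Aim 1 says how the nine final tests will be judged, and no stepwise or closed procedure is mentioned. A separate analysis plan may settle this; it is not at hand.

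**The concern.** A single cut-off of 0.05/9 treats the nine null hypotheses as if any subset of them could be true. Within one outcome that is not so. If two of the three arm means are equal to each other and one of those equals the third, all three are equal, so exactly two true pairwise nulls cannot occur. Once one pair has been shown to differ, at most one of the other two nulls can still be true. A fixed z = 2.77 for those remaining pairs guards against an error pattern that is impossible.

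What is at stake is power, not validity. It matters most for Hypothesis 1 (end of the Background section), which sets Arm 3 against Arms 1 or 2. If that is read as Arm 3 beating both, two contrasts must be rejected for the same outcome, and a strict second cut-off costs most there.

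**Working it through.** **Inputs from the article.** Experiment-wise error 0.05; nine tests; z = 2.77; variance of BMI percentile 18.8, so SD = √18.8 = 4.336; difference 1.67, which is 1.67/4.336 = 0.385 SD; 525 children, 175 per arm; 15% attrition, which leaves 0.85 × 175 = 148.75 per arm. The ICC value is missing from the text available, so it is not used.

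**The plan's own figures.**
- Two-sided 0.05/9 = 0.00556 gives z = 2.773, so the stated cut-off is plain Bonferroni.
- Detectable difference = (2.77 + 0.842) × 4.336 × √(2/175) = 1.674. This agrees with the stated 1.67, at 175 analysed per arm.
- Power at 0.385 SD with 175 per arm: 0.385/√(2/175) = 3.601, and Φ(3.601 − 2.773) = 79.6%.
- Power at 0.385 SD with 148.75 per arm: 0.385/√(2/148.75) = 3.320, and Φ(3.320 − 2.773) = 70.8%. This assumes no precision gain from the repeated-measures model.

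**The alternative rule.** Within each outcome, at level 0.05/3 = 0.0167: reject the largest of the three pairwise |z| if it exceeds 2.77. If it does, reject either remaining pair whose |z| exceeds 2.39, the two-sided 0.0167 point.

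**Error control within one outcome.**
- All three nulls true: an error needs the largest |z| to exceed 2.77, with probability at most 3 × 0.00556 = 0.0167.
- Exactly one null true: an error needs that pair's |z| to exceed at least 2.39, with probability at most 0.0167.
- Exactly two nulls true: impossible.
- No null true: no error can be made.

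So each outcome costs at most 0.0167 and the three together at most 0.05, whatever the correlation between outcomes. Simulation (1,000,000 replicates) gave 0.0155 to 0.0157 per outcome under the complete null and at most 0.0167 with one true null. Any pair with |z| above 2.77 is rejected under both rules, so no rejection is lost.

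**Power at 0.385 SD, normal approximation, simulated.**

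| True pattern | Analysed per arm | Contrast | z = 2.77 throughout | Step-down |
|---|---|---|---|---|
| Arm 1 = Arm 2, Arm 3 better | 175 | each Arm 3 contrast | 79.6% | 85.5% |
| same | 175 | both Arm 3 contrasts | 68.2% | 79.9% |
| same | 148.75 | each Arm 3 contrast | 70.8% | 77.5% |
| same | 148.75 | both Arm 3 contrasts | 56.6% | 70.0% |
| Arm 2 midway | 175 | 3 vs 1 | 79.6% | 80.4% |
| Arm 2 midway | 148.75 | 3 vs 1 | 70.8% | 71.9% |
| Arm 2 one third of the way | 148.75 | 3 vs 1 | 70.9% | 72.6% |
| same | 148.75 | 3 vs 2 | 28.8% | 40.0% |
| Equal steps of 0.385 SD | 148.75 | adjacent pairs | 70.8% | 82.3% |

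**What the gain is worth.** For 77.5% power per contrast with z = 2.773 throughout, the analysed number is 2 × (2.773 + 0.755)²/0.385² ≈ 168 per arm. Against 149 per arm that is 3 × 19 = 57 more analysed children.

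**The case against.** The strongest reply is that nothing here is wrong. The article uses z = 2.77 to determine sample size, calls it conservative itself, and fixes no decision rule for the final tests. Sizing with Bonferroni and analysing with a step-down test is compatible with every sentence it contains. That stands. The loss arises only if the sizing cut-off is reused, and what is offered is a better rule than the only one stated.

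Three further objections also stand in part.

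- **The gain is not uniform.** A gain of 6 to 7 points per contrast needs Arm 2 to equal Arm 1 or Arm 3, and the article assumes neither. With Arm 2 midway, Arm 3 vs 1 gains about 1 point. The gain of nearly 12 points in adjacent pairs needs an Arm 3 vs 1 difference of 0.77 SD, twice the planned effect.
- **The single-step rule does buy something.** With an Arm 3 effect on all three outcomes its actual experiment-wise error is about 0.017, against about 0.049 for the step-down. Its tests also always agree with its simultaneous intervals. But the plan asks for 0.05, not less.
- **The baseline depends on an unseen figure.** A reader might infer that power after attrition is really 71% rather than 80%. The article does not support that. Its 80% is stated with attrition included and draws on an ICC whose value is missing from the text. If adjustment for baseline with an assumed correlation r reduced the variance by 1 − r², power per Arm 3 contrast at 148.75 per arm (Arms 1 and 2 equal) would go from 80.2% to 85.9% at r = 0.4, from 91.5% to 94.9% at r = 0.6, and from 99.7% to 99.9% at r = 0.8. Whether 1.67 holds after attrition is a separate question from multiplicity.

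**Conclusion.** The point holds as an efficiency improvement, conditional on z = 2.77 being carried into the final tests. The stated cut-off controls the error rate and is not a mistake. Among rules that meet the plan's own 0.05 target, the step-down rejects everything the fixed cut-off rejects and sometimes more.

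With Arms 1 and 2 equal and a 0.385 SD advantage for Arm 3, the gain is about 6 points per Arm 3 contrast at 175 analysed per arm. It is about 7 points at 148.75 per arm if the repeated-measures model adds nothing. For rejecting both contrasts it is about 12 and 13 points. Across the other patterns examined, single-contrast gains run from about 1 to about 12 points. The power figures rest on normal approximations and equal arm sizes; the error bound does not depend on the effect pattern.

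**What to change.** Before unblinding, add one sentence to the analysis plan, unless it already fixes an equivalent rule: within each primary outcome, at level 0.05/3, the largest of the three pairwise statistics is compared with two-sided 0.05/9 (z = 2.77); if it is rejected, the other two pairs are each tested at two-sided 0.0167 (z = 2.39), following Shaffer's step-down for three groups. The section on blinding describes the biostatistician as unblinded, so the sentence should be dated and filed before anyone compares outcomes by arm.

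Keep z = 2.77 in the sample-size statement and for the simultaneous intervals. No child is added and no procedure changes. The one cost is in reporting: a pair rejected at the second step can have a 99.4% interval that includes zero, so the report must say that decisions are step-down and that the intervals are the wider single-step ones.

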#### Aim 1 (Primary Outcomes): Examine intervention effects on markers of child CVH including BMI%ile, diet quality, neck circumference.

Treatment condition mean differences on the three primary outcomes will be examined at the post-intervention primary endpoint (6 months after baseline). Sample size determination allows for primary outcome standardized effect size assessment of all three outcomes of at least 0.38, which is a small-to-moderate minimum detectable effect.

#### Aim 2 (Secondary Outcomes): Examine intervention effects on family, parental, and sibling factors.

Family meal quantity and quality, food parenting practices and stress, and sibling BMI %ile outcomes are powered at similar levels as in Aim 1 with the ability to detect standardized effect sizes as small as 0.38.

#### Sub-group Exploratory Analyses:

Analyses exploring whether interaction effects depend on participant sex, race/ethnicity, and seasonality will also be conducted. These post-hoc analyses will examine whether the intervention has synergistic effects in specific populations or during different seasonal contexts. Post-hoc analyses will be conducted to explore the interaction of child/parent sex and baseline weight status on intervention treatment effects to determine whether the intervention is particularly effective in certain subpopulations.

#### Other Exploratory Hypotheses:

A model incorporating an interaction effect of treatment arm crossed with the change in family meal quality and quantity between observation periods will be used to evaluate if increases (or decreases) in the quality and quantity of family meals correspond with synergistically favorable (or unfavorable) child outcomes. This analysis will inform whether intervention effects depend on participants’ changes in family meal quality and quantity. This analysis is powered to detect a between-within intervention slope difference over the 6-month intervention period of as little as 9.6 ounces per month, depending on whether participants had high or low change in the moderating variables. Seasonality robustness checks will also be performed to evaluate whether results differ substantively for participants who received the intensive intervention during the summer months.

